## **5.2. Concomitant Medications (CONMED)**

Participants will be asked to remain on stable dosages of concomitant psychotropic medications. Changes to treatment regimens or the introduction of psychotherapy, however, will not be permitted during the acute intervention phase of the trial (4-week/ 28 days), 4 weeks (28 days) before the start of the trial, and during the 4-week (28 days) follow-up period. If changes to treatment regimens or the introduction of psychotherapy are determined to be required as per the patient's standard of care, the required changes will be made, and the participant will be withdrawn from the study.

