Eligible participants enrolled in this clinical trial will have a total of 28 visits. There will be 1 screening visits which will take place over the phone, 3 on-site visits (including 1 mask development visit, 1 mask delivery visit, and 1 very last follow-up visit) and 24 On-line visits (to take place over videoconference on Zoom platform); Baseline Visit (Visit 0), 20 days of the FES treatment sessions (Visits 1-20), and three post-stimulation visits (Visits 21-23). The screening Visit will take about 90- minutes, the on-site mask development visit will take 40 minutes and the mask delivery Visit will take 60-90 minutes. The baseline Visit (Visit 0) will take approximately 45 minutes, and treatment days (Visits 1-20) will take 60 min each (45 min for stimulation and 15 min for preparations). Sessions 5, 10, 15, and 20 will last about 105 minutes and will include similar clinical assessments/questionnaires to the baseline visit. The post-stimulation visits will take approximately 45 min. We estimate that the total participation duration will be approximately 33 to 35 hours.

Prior to the baseline visit, participants will undergo a screening evaluation that includes a medical/treatment history assessment and a confirmation of the MDD diagnosis. If all inclusion criteria are met, the mask development visit, the mask delivery visit, and the baseline visit will be scheduled. During Visit 0, medical assessments will be performed, and baseline assessments consisting of a semi-structured interview and self-report scales will be conducted. Once all baseline measures are collected, participants will be randomly assigned to one of two treatment arms:

- **ARM 1. 40 Hz FES:** 40 Hz Functional Electrical Stimulation (FES) stimulation, 45 mins per day for the duration of 4 weeks (20 sessions).
- **ARM 2. Sham FES:** 45 mins per day for the duration of 4 weeks (20 sessions).

Patients who miss a treatment visit, including due to statutory holidays, will be flagged in the database as non-adherent but will not be withdrawn from the study. They will still receive the entire treatment schedule but over a longer time period. However, if subjects miss more than two treatment days during treatment Days 1-20, they will be withdrawn.

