#### Post-Stimulation Follow-Up Visits (Visits 21-24)

Visit 21 will take place within 1 week after Day 20 of treatment. The study team will aim to schedule the appointments as close as possible to the last FES study visit (Day 20). Subsequent visits will take place two, three, and four weeks after Day 20 of the intervention. Visits 21 to 23 will take place over videoconference and Visit 24 will happen on-site. Each follow-up visit will consist of the following:

- Psychiatric interview
  - Hamilton Depression Rating Scale 17-Item (HAM-D-17)
- Self-report scales using REDCap
  - 16-Item Quick Inventory of Depression Symptomatology (QIDS-SR-16)
  - Generalized Anxiety Disorder-7 Scale (GAD-7)
  - World Health Organization-5 Well-Being Index (WHO-5)
  - Pittsburgh Sleep Quality Index (PSQI)
- Assessment of CONMED record
- Assessment of FES Expectancy- will be completed with the subject using REDCap
- Review of FES side effects and adverse events

In the last follow-up visit (Visit 24) participants will return the stimulators and any unused electrode but they can keep the personalized masks. If participants do not complete the entire study, we may ask them to return to St. Michael's Hospital for some of the follow-up visits, including a psychiatric interview, self-report scales, and/or neuropsychological testing.

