### **10.3. Early Withdrawal**

Participants are free to withdraw their consent and stop research study participation at any time without penalty or loss of benefits to which they are otherwise entitled. A participant's doctor may withdraw them from the study if he/she feels that it is in their best interest. The Principal Investigator may also decide to terminate the study at any time if the stimulation device is believed to be unsafe.

A study participant will be discontinued from further participation if:

- The participant fails to adhere to the study procedure.
- The participant decides not to be in this study.
- The participant misses more than two treatment visits.
- They experience worsening in depression, defined as an increase in QIDS-SR-16 score from baseline of more than 25% during two consecutive assessments, or development of active suicidal intent or attempted suicide.
- The participant meets any exclusion criteria (either newly developed or not previously recognized).

- Anything, in the opinion of the investigator, would place the participant at increased risk or preclude the participant's full compliance with or completion of the study.

If a participant withdraws or is withdrawn from the study, they will be asked questions about their experience with the FES stimulation. They will also be asked to cooperate with whatever laboratory tests or medical examinations the doctor considers necessary.

We will collect safety data on any participant discontinued because of an AE or SAE. In any case, every effort will be made to undertake protocol-specific follow-up procedures. If an AE has been reported, researchers will help the participant seek the medical care they need, and a follow-up will be performed by the Principal Investigator. In the case of an early withdrawal, the researcher will make a note to file indicating this.

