## **14.2. Clinical Outcomes Analysis**

We are primarily interested in precise estimates of tolerability, outcome variability, and preliminary effectiveness of FES compared to sham FES in patients with MDD that will aid in the planning of a larger, sufficiently powered efficacy trial.

Initial analyses will summarize socio-demographic and clinical characteristics by treatment group. Primary analyses will be performed on the modified intention-to-treat (ITT) population, including all randomized participants that received at least one FES treatment. The feasibility outcome defined as overall dropout rates will be summarized using descriptive statistics such as counts and percentages. Feasibility analyses will report feasibility outcomes using descriptive statistics with counts and proportions for categorical data and means and standard deviations or median and interquartile range, as appropriate, for continuous data. The proportion lost to follow-up will be estimated along with a 95% confidence interval. The lower 95% confidence limit should be at least 90% to proceed. The proportion compliant with the protocol, including treatment compliance as well as study completion and complete data on clinical outcomes will be estimated with 95% confidence interval. For validity to be fairly high, the lower 95% confidence limit should be >90%. The blinding index proposed is scaled to an interval of -1 to 1, 1 being a complete lack of blinding, 0 being consistent with perfect blinding and -1 indicating opposite guessing, which may be related to unblinding.

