The preliminary effectiveness analysis will report the between group difference in change from baseline to treatment 20 in the HAM-D-17 and its 95% confidence interval, using analysis of covariance (ANCOVA), with 20 treatment HAM-D-17 as the outcome and baseline HAM-D-17 and stratification variables (sex) as covariates. We will also report estimates for standard deviation of HAM-D-17 score and within-person correlation between baseline and follow-up HAM-D-17 scores. A similar approach will be used for all other continuous variables for secondary outcome measures (e.g., QIDS-SR, GAD-7, etc). Differences between groups in dichotomous outcomes (e.g., response, remission, adverse effects) will be described using an odds ratio and 95% confidence interval. To explore the sustainability of the treatment effect, we aim to also report changes of HAM-D-17 scores during the month after 20 treatments. The success of blinding of patients will be assessed by computation of Bang's blinding index. Sex and gender stratified analysis will be carried out.

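### Participants withdrawn for worsening, a treatment change or more than two missed sessions are not guaranteed a treatment-20 HAM-D-17, so the single-visit ANCOVA risks becoming a completer analysis

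*Protocol*

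**What the plan says.** **Removal from the study.** Three kinds of event end participation as a whole:
- Worsening (Section 10.3, repeated in 6.1): "They experience worsening in depression, defined as an increase in QIDS-SR-16 score from baseline of more than 25% during two consecutive assessments". Active suicidal intent or attempted suicide also counts.
- A treatment change needed under standard care (Section 5.2): "the required changes will be made, and the participant will be withdrawn from the study". This covers both the treatment phase and the four-week follow-up.
- Missed sessions (Section 6.1, also 5.4 and 10.3): "if subjects miss more than two treatment days during treatment Days 1-20, they will be withdrawn".

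**Assessment after removal.** Section 10.3 promises, in general terms, best efforts to carry out the protocol's follow-up procedures. The section on the post-stimulation visits is weaker: "If participants do not complete the entire study, we may ask them to return" for some of those visits, with a psychiatric interview and self-report scales among the possibilities.

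**Analysis.** Section 14.2 places primary analyses in a "modified intention-to-treat (ITT) population, including all randomized participants that received at least one FES treatment". It estimates the HAM-D-17 effect "using analysis of covariance (ANCOVA), with 20 treatment HAM-D-17 as the outcome and baseline HAM-D-17 and stratification variables (sex) as covariates". The same section reports the HAM-D-17 SD and the within-person correlation for planning a larger trial. Section 6.3 and Table 1 also schedule HAM-D-17 at Visits 5, 10 and 15.

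**Missed visits.** Under Section 6.1, participants who miss a visit, "including due to statutory holidays, will be flagged in the database as non-adherent", stay in the trial and receive the full schedule over a longer period.

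**The concern.** A participant with no treatment-20 HAM-D-17 cannot enter the stated model, whatever the analysis population is called. Some of the removal triggers depend on how the participant is doing, so the missing scores need not resemble the observed ones. An analysis plan written later can choose how to handle missing data, but it cannot recover ratings that were never taken.

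Three results are exposed:
- **Effectiveness.** The arm difference, the SD and the baseline-to-follow-up correlation would come from the reduced set. Section 14.2 wants these quantities for planning the next trial.
- **Dropout and compliance.** These are primary outcomes (Section 8.1). A removal required by the protocol and a participant's own decision to leave fall into the same rate, although they say different things about tolerability. A flag for a public holiday says nothing about the participant.
- **Sustainability.** A treatment change during follow-up also ends participation, so the later HAM-D-17 scores come from participants who needed no change.

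**Working it through.** **1. The passages side by side**

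| Event | What ends | Treatment-20 HAM-D-17 secured? |
|---|---|---|
| Worsening (10.3, 6.1) | further participation | no |
| Treatment change before Visit 20 (5.2) | the study | no |
| Treatment change during follow-up (5.2) | the study | already obtained; only later scores are lost |
| More than two sessions missed (6.1, 5.4, 10.3) | the study | no |
| One or two sessions missed (6.1) | nothing | yes, participant stays |

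The best-efforts sentence in Section 10.3 names no rating or time point. The optional return in Section 6.3 concerns visits after treatment 20.

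**2. The plan's own figures**

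Section 5.3 says a 15% dropout allowance is in the sample size calculation. Section 14.1 gives only the total of 20, with no effect size, SD, power or precision target, so 20 cannot be re-derived. It is arithmetically consistent with 17 completers: 20 × 0.85 = 17 and 17 / 0.85 = 20. That leaves 3 participants without a treatment-20 score.

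**3. Shift in one arm's mean**

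Input: SD of HAM-D change 5.26, from the earlier open-label study in Section 3. If the worst fraction p of an arm is missing and change is normal, the mean of the remainder moves by

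SD × φ(z) / (1 − p), with z = Φ⁻¹(1 − p).

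- p = 0.10: 1.03 points
- p = 0.15: 5.26 × 0.2332 / 0.85 = 1.44 points
- p = 0.20: 1.84 points
- p = 0.30 (3 of 10): 5.26 × 0.3477 / 0.70 = 2.61 points

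**4. Shift in the ANCOVA difference**

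The Section 14.2 model was simulated with 10 per arm and 20,000 runs per scenario. Change SD was 5.26. Baseline mean 18, baseline SD 4 and mean change −6 are assumptions. The participants with the worst change lack the treatment-20 score. The difference is active minus sham, so negative favours active.

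| Lost, active | Lost, sham | Shift | Estimate when the true difference is −4: full data → observed |
|---|---|---|---|
| 0 | 3 | +2.4 | −4.02 → −1.63 |
| 1 | 2 | +0.8 | −3.98 → −3.22 |
| 2 | 1 | −0.8 | −4.01 → −4.79 |
| 3 | 0 | −2.4 | −4.01 → −6.41 |
| 1 | 1 | about 0 | −3.99 → −3.99 |
| 2 | 2 | about 0 | −4.01 → −4.01 |
| 0 | 3, at random | about 0 | not run (shift found with no true effect) |

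The shifts are the same with no true effect. They agree roughly with step 3: 2.61 for three lost from one arm, and 1.84 − 1.03 = 0.81 for a 2:1 split. If every withdrawn participant still has a treatment-20 HAM-D-17, the shift is 0.

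**5. Holidays and compliance**

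No arithmetic applies. Section 6.1 attaches a non-adherence flag to a session missed for a statutory holiday. Section 14.2 asks for a lower 95% limit above 90% on protocol compliance, treatment compliance included. If the flag feeds that proportion, a calendar effect lowers it. The Protocol does not say whether it does.

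**The case against.** A reader might infer that the effectiveness estimate simply is a completer analysis that discards those who did badly. The text does not fix that. Section 10.3 promises best efforts at follow-up, so a withdrawn participant may still supply a treatment-20 rating. Missing-data handling may sit in an analysis plan that is not shown. A treatment change or missed sessions need not mean a poor outcome.

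A reader might also infer a flat contradiction with intention to treat. Section 14.2 ties that population to primary analyses, while HAM-D-17 is secondary. Its use for the ANCOVA is implied, not stated.

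A baseline-adjusted endpoint ANCOVA is standard for a secondary, estimation-only outcome in a pilot of 20. A repeated-measures model repairs only part of the loss. In a separate 500-trial simulation with a true difference of 4, the mean differences were 4.17 on full data, 3.54 in completers and 3.91 with repeated measures. The SDs across trials were 3.24 for completers and 3.13 for repeated measures. That simulation used a stand-in withdrawal rule and losses of about 26% (active) and 38% (sham), well above the stated 15%.

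On missed visits, those affected are "flagged in the database as non-adherent but will not be withdrawn from the study", so holidays do not by themselves bias the ANCOVA.

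These points limit the claim, and the model change is secondary to collecting the rating. They do not supply a commitment to the treatment-20 rating, and they do not reconcile the two differing follow-up statements.

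**Conclusion.** The point holds as a risk that the Protocol leaves open. Participants leave the study for reasons partly related to outcome, no passage guarantees them a treatment-20 HAM-D-17, and the stated model cannot use anyone without one.

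The size is illustrative. At the stated 15% dropout, with an SD of 5.26 and the worst responders lost, the arm difference shifts by up to about 2.4 points in either direction. It shifts by about 0 when loss is balanced, random or fully followed up. A claim that the bias favours one arm would go beyond the documents.

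Importance is moderate. The outcome is secondary in a 20-person pilot, but its estimates are meant to plan the next trial, and the same removals enter the primary dropout and compliance rates. The holiday flag is a smaller, separate defect in the compliance outcome.

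It is also unclear what counts as consecutive assessments in the worsening rule. Section 6.3 and Table 1 schedule QIDS-SR-16 daily, whereas Section 6.1 states the rule shortly after describing assessments every five treatment days. How often the rule would be met in stable participants depends on day-to-day variability that the Protocol does not give, so no rate is claimed.

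**What to change.** 1. Reconcile Sections 5.2, 6.3 and 10.3 by separating the end of stimulation from the end of study participation. Keep the scheduled HAM-D-17 and QIDS-SR-16 video assessments, at least the one at the treatment-20 time point, for everyone randomized unless consent is withdrawn. This is the main remedy.
2. Use the HAM-D-17 scores from Visits 5, 10, 15 and 20 in a repeated-measures model adjusted for baseline and sex, with the contrast at Visit 20. It can be the main estimate or stand beside the ANCOVA.
3. Report protocol-mandated discontinuations separately from participant-initiated dropout, and do not count statutory holidays as participant non-adherence.
4. Ask the clinical team to reconcile the wording on consecutive assessments with the daily QIDS-SR-16 schedule. No clinical rule is proposed here.

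The cost is wording and a few extra video ratings. The model uses scores already scheduled; its downside is slightly more complexity at n = 20.

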#### Functional Electrical Stimulation Improves Symptoms of Major Depressive Disorder

Kapadia et al. (2019) conducted a follow-up open-label mixed-methods study on individuals with MDD, where they wanted to explore whether 10 sessions of the FES would lead to improvements in depressive symptoms. This study recruited 10 individuals with moderate-to-severe MDD, and all study participants received facial FES of the “Duchenne” muscles three times per week for a minimum of 10 sessions and a maximum of 40 sessions. All participants received 10 sessions of the FES and were invited to continue therapy for up to 40 sessions if they wished (5 out of 10 participants requested to undergo 40 FES sessions). The results were promising: participants experienced early improvements in depressive symptoms as measured by the Hamilton Depression Rating Scale (HAM-D) and Inventory of Depressive Symptomology (IDS) upon

completing 10 sessions of treatment. On average, the participants showed an improvement on the HAM-D by 8.1 points (SD = 5.26,  $p = .005$ ) and on the IDS by 14 points (SD = 11.05,  $p = .008$ ). Eighty percent of participants showed a reduction by at least 30%, 50% achieved clinical response (i.e., change in the HAM-D by at least 50%), and 60% entered remission. The reported adverse events were insignificant, involving commonly reported redness or skin irritation underneath the stimulation site, muscle soreness, and muscle discomfort. All participants enrolled in the trials adhered to the treatment protocol, showing high compliance. FES was well-tolerated, with the potential to be administered with limited physician oversight.

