### **5.3. Method of Recruitment**

The single study center will be the Interventional Psychiatry Program at St. Michael's Hospital, Unity Health Toronto (SMH, UHT). The subjects will be recruited from the Interventional Psychiatry Program at St. Michael's Hospital, Unity Health Toronto. The target recruitment rate is a total of 20 subjects recruited over 6 months. Considering our prior experience with this type of study, we do not anticipate any significant compliance issues. We note that the 5 sessions per week proposed here exceeds the schedule in the preliminary study by 2 sessions per week with the presence of a sham arm; we have included a conservative 15% dropout rate in our sample size calculations. However, a 5 session per week schedule is well tolerated in rTMS for MDD and in FES for stroke rehabilitation. Notably, since the intervention includes monitored home-based visits, treatment adherence will be known with 100% accuracy.

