**Table 1: Study Schedule**

## 6.2. Randomization and Blinding

Participants will be randomized in a 1:1 allocation to receive FES (active pattern) or FES (sham pattern). Block randomization will be computer-generated, and the samples will be stratified for sex, given the potential differences in response and tolerability in these groups. A biostatistician will generate the randomization schedule, to be administered by a research assistant who is not associated with the study and instructed not to divulge group assignments to the participants to allow for concealment.

Participants and most study staff will be blinded. Only the physical therapist will need to monitor the participant. Measures taken to prevent functional unblinding include sensory and non-patterned sham and delivering automated messages to both active and sham groups. We will also evaluate each participant's ability to discriminate what treatment they received after each session to assess blinding effectiveness.

We will randomize subjects to study arms (20 days active or 20 days sham) using a secure online randomization module on REDCap. The block size will be fixed, and study personnel will be blinded to the randomization block size. An independent assistant, external to the study, will manage the randomization of subjects. The subject number and treatment code will be assigned

after the subject details have been obtained. Based on this information, the independent assistant will assign a unique subject number and treatment code, which will dictate the treatment assignment for the subject. The patterns will be pre-programmed into the take-home device by the biomedical team.

An unblinded code sheet that matches these stimulation codes to the treatment arm will be kept by an external coordinator and will not be available to the study coordinator or research assistants. The unblinded code sheet will have the following information:

1. The initial identifier codes for all potential participants
2. Stimulation code: 6-digit numerical code for the stimulation session
3. Condition number: Numerical code for the condition
4. Condition name: Name of the condition

A copy of this code sheet with the condition name removed will be provided to the study coordinator and research assistants. These linked codes ensure that the study coordinator and research assistants are kept blinded to the type of treatment each participant will receive.

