## **8. Outcome Measures**

### **8.1. Primary Outcome Measures**

The primary outcome will be the feasibility, tolerability, and safety outcomes that include the recruitment, dropout, data completion, and protocol compliance rates, as well as the number and nature of AEs and SAEs. Self-report questionnaires will be completed via REDCap.

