### **14. Data Analysis**

#### **14.1. Sample Size Considerations and Study Feasibility**

For this pilot feasibility trial, we aim to recruit 20 participants in total.

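### An odds ratio is a poor sole between-arm measure for sparse or near-universal adverse events at about 10 per arm; add a risk difference with a score-based interval

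*Protocol*

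**What the plan says.** Protocol Section 14.2 states the between-arm measure for all binary outcomes in one sentence: "Differences between groups in dichotomous outcomes (e.g., response, remission, adverse effects) will be described using an odds ratio and 95% confidence interval". No absolute difference between arms is planned for them.

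The same section gives the purpose of the analysis: "We are primarily interested in precise estimates of tolerability, outcome variability, and preliminary effectiveness of FES compared to sham FES", as input to a larger trial. It also plans a descriptive summary: "Feasibility analyses will report feasibility outcomes using descriptive statistics with counts and proportions for categorical data". Section 8.1 places adverse events in the primary outcome, "as well as the number and nature of AEs and SAEs".

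On size, Section 14.1 says "we aim to recruit 20 participants in total" and Section 6.2 says "Participants will be randomized in a 1:1 allocation", so there are about 10 per arm. Section 5.3 adds that "we have included a conservative 15% dropout rate in our sample size calculations".

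On expected rates, Section 3 reports 50% response and 60% remission among the 10 participants of the open-label pilot in MDD. Of safety in that pilot it says "The reported adverse events were insignificant, involving commonly reported redness or skin irritation underneath the stimulation site". Section 9.2 instead says that the earlier FES studies produced no adverse events. The protocol gives no expected sham response or remission rate and no expected SAE rate.

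**The concern.** A sample odds ratio is a finite, non-zero number only if all four cells of the 2×2 table are occupied. If one arm has no events, or only events, the estimate is 0 or infinite. If both arms have none, or both have all, it is 0/0. With about 10 per arm, empty cells are likely whenever the true risk is close to 0 or 1, and that is where safety outcomes may well lie.

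At stake is the between-arm statement on tolerability. Adverse events belong to the primary outcome, and the section aims at estimates that a planner of the next trial can use. For SAEs the only between-arm measure named would often yield no estimate. For uncommon adverse events it would often yield only a 0 or an infinity.

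**Working it through.** The protocol states no precision or event-count figure for binary outcomes, so there is none to reproduce. The check is an exact binomial calculation.

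**Inputs**
- n = 10 per arm (Sections 14.1 and 6.2). A 15% loss (Section 5.3) would leave 8.5, so n = 8 is used as a sensitivity case.
- Active response 50% and remission 60% (Section 3, pilot).
- Assumptions not in the protocol: SAE risk 1% to 5% in each arm; risk of a given adverse event 10% to 15% in both arms, with 90% as the near-universal case; sham response or remission 10% to 50%.

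**Formulas**, for risks p₁ and p₂ with n per arm:
- P(at least one empty cell) = 1 − (1 − a)(1 − b), where a = p₁ⁿ + (1 − p₁)ⁿ and b = p₂ⁿ + (1 − p₂)ⁿ.
- P(0/0) = (1 − p₁)ⁿ(1 − p₂)ⁿ + p₁ⁿp₂ⁿ.

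**SAEs, n = 10**
- Risk 5%: 0.95¹⁰ = 0.599, so P(empty cell) = 1 − 0.401² = 0.839; P(0/0) = 0.95²⁰ = 0.358.
- Risk 1%: 0.99¹⁰ = 0.904, so P(empty cell) = 1 − 0.096² = 0.991; P(0/0) = 0.99²⁰ = 0.818.

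**Adverse events with the same risk in both arms, n = 10**
- Risk 15%: 0.85¹⁰ = 0.197, so P(empty cell) = 1 − 0.803² = 0.355; P(0/0) = 0.039.
- Risk 10%: 0.90¹⁰ = 0.349, so P(empty cell) = 1 − 0.651² = 0.576; P(0/0) = 0.122.
- Risk 90%: by symmetry, 0.576 and 0.122.

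**Response and remission, P(empty cell)**

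| Active rate | Assumed sham rate | n = 10 | n = 8 |
|---|---|---|---|
| 50% (pilot response) | 50% | 0.4% | 1.6% |
| 50% | 30% | 3.0% | 6.5% |
| 50% | 20% | 10.9% | 17.4% |
| 50% | 10% | 35.0% | 43.5% |
| 60% (pilot remission) | 30% | 3.4% | 7.4% |
| 60% | 20% | 11.3% | 18.2% |
| 60% | 10% | 35.3% | 44.0% |

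In all these rows P(0/0) is 0.2% or less.

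**What a risk difference gives at 10 per arm**

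The Newcombe interval combines the two Wilson intervals. For 0/10 the Wilson upper limit is z²/(n + z²) = 3.84/13.84 = 0.278.
- 0/10 v 0/10: difference 0, from −27.8 to +27.8 points.
- 1/10 v 0/10: +10, from −18.9 to +40.4 points.
- 5/10 v 2/10: +30, from −10.7 to +60.0 points. The odds ratio for this table is (5 × 8)/(2 × 5) = 4.0, with standard error of its logarithm √(1/5 + 1/5 + 1/2 + 1/8) = 1.012 and Wald 95% CI 0.55 to 29.1.
- An arm with 0/10 has an exact 95% upper limit of 1 − 0.025^(1/10) = 30.8%.

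The risk difference and its interval therefore exist for every possible table.

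**The case against.** The strongest reply is that the protocol names a measure, not an estimator. Exact or penalised intervals for empty cells are commonly left to a statistical analysis plan, and a conditional exact interval would comply with Section 14.2 as written. That stands: the absence of an empty-cell method is not itself a fault. The choice of measure, however, has been made in the protocol, and for a 0/0 table even an exact interval for the odds ratio runs from zero to infinity and carries no information.

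Several stronger readings might be inferred, and the protocol does not support them:
- *The odds ratio is the only summary.* It is the only between-arm measure. Counts and proportions are planned for categorical feasibility outcomes, and adverse events are to be reported by number and nature.
- *Every table with an empty cell is unusable.* One empty arm still leaves an exact interval with one finite, informative limit. Only 0/0 tables leave nothing. For a 10% to 15% adverse event in both arms that is 12.2% to 3.9% of trials, not 58% to 36%.
- *The protocol expects nearly every active participant to have an adverse event.* Section 3 speaks of common skin reactions, but Section 9.2 says the earlier studies saw no adverse events. The rate is open at both ends.
- *Response and remission will often fail.* At the pilot's rates they do so only if the sham rate is near 10%, which the protocol does not state.

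Two further points are fair. The sentence in Section 14.2 does not name SAEs; they enter as one kind of adverse effect under an open list. Hypothesis 1b concerns the overall number of events, so the odds ratio is not clearly its analysis. Finally, no progression rule in Section 14.2 depends on the odds ratio, and no measure is precise at 10 per arm.

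**Conclusion.** The point holds for sparse or near-universal events. For SAEs at assumed risks of 5% to 1% per participant, at least one arm has no event in 84% to 99% of trials, and the odds ratio is wholly undefined in 36% to 82%. For an adverse event at an assumed 15% to 10% in both arms, the estimate is 0, infinite or undefined in 36% to 58%. For response and remission at the pilot's rates the problem is small: about 0.4% to 11% for assumed sham rates of 50% to 20%.

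These figures rest on 10 per arm, independent participants and assumed SAE, adverse-event and sham rates; only the 50% and 60% come from the protocol. With 8 per arm the empty-cell figures are higher, for example 88.7% to 99.4% for SAEs at 5% to 1%.

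This is a modest improvement to the reporting of tolerability, not an error that threatens the trial. A reader might infer that the odds ratio should be deleted. The calculation does not show that, since dropping it altogether is a preference about effect scale.

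**What to change.** In Section 14.2, state that each binary outcome will be reported as the count and proportion in each arm with an exact 95% CI, and as the risk difference between arms with a Newcombe or other score-based 95% CI. Keep the odds ratio as a supplement only, with a conditional exact interval.

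This takes about one sentence and no new data. The downside is one more effect measure to report for each outcome.
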